### Data collection, management, and quality control

Paper surveys for patients and GPs are used to increase the cooperation of GPs and patients during the trial, according to local experts in the study group. However, all paper surveys were created using the software program evasys [21], so that an automatic export of the survey answers at the study center of the participating university hospital (UMG) will be possible for the subsequent evaluation at Charité – Universitätsmedizin Berlin (Charité). The patient and GP paper surveys will be picked up once a month from the GP offices by UMG study personnel.

The standardized telephone interview at 3-month follow-up for patients will be based on a survey, pre-programmed in an evasys web surface, which will be filled out by the interviewer during the call. Since we are expecting attrition to occur, especially at the 3-months follow-up, reasons for dropouts and loss-to-follow-up will be collected.

The NeTKoH-database was programmed using automatic plausibility checks and mandatory fields for data entry. Technical training of the GP offices regarding the use of the teleconsulting system will take place prior to the start of the intervention. On-site monitoring, a feedback loop, and measures to inquire regarding implausible or missing data by the study personnel will be instituted. The study personnel will receive training for the documentation in the NeTKoH database and the evasys web surface. All surveys were piloted before the start of the intervention.

All data collection, handling, transferring, processing and storage will follow the project’s comprehensive data protection concept approved by the responsible data protection officers. The primary and secondary data of NeTKoH will be securely transferred from the data integration center at UMG to the independent evaluation team at Charité for the final analysis and provision of findings to the funding agency. Trained researchers of the evaluation team will code, enter and store the data on the secure Charité server. Only the evaluation team will have access to the final data set.

### Statistical methods: sample size and power calculations.

The study includes 33 clusters in the region of West Pomerania, in which the participating university hospital is located. Sample size calculations were based on the Hussey & Hughes approach [22] for stepped-wedge cluster design for analysis with fixed time effects and random cluster effects.

The sample size calculation was based on the primary endpoint. As a basis for this calculation, we took the assumption that in the control group, the proportion of outpatient neurological symptoms that can be solved in the GP's practice (i.e., there is no subsequent neurological or special outpatient consultation or inpatient referral) is 0.2 (20%). We expect a 50% improvement (i.e., a 50% increase in effect size on the risk difference scale) in the intervention group, corresponding to an expected proportion of 0.3 (30%) in the intervention group.

With a total sample size of 1,089 participants (corresponding to 555 patients included in the control phase and 534 patients included in the intervention phase) at a type I error rate of 0.05, and an assumed coefficient of variation of 0.25, the study has a power of 80%, at a coefficient of variation of 0.20 and a power of 81% to measure the assumed effect size or a larger effect. Due to the nature of the intervention and the immediate collection of the primary endpoint data following the intervention, no attrition pertaining to this endpoint can be expected.

To achieve this number of cases, the stepped-wedge cluster randomized trial (CRT) must recruit, on average, at least 3 patients meeting the inclusion criteria, per cluster and step, to perform an appropriate analysis for this design.

To examine secondary endpoints (except those using claims data), all patients included during the study can be analyzed. Based on an estimate from experts of the NeTKoH study group, we assume an average demand of 6 to 8 neurological consultations per GP per month, which means about 3,168 neurological consultations per year in the whole region. Of these, about 25% of patients* (N = 792 per year, N = 66 per month) are insured by the participating statutory health insurances AOK Nordost and Techniker Krankenkasse. Assuming a loss of 30% due to non-participation or loss-to-follow-up, complete data of about 554 neurological consultations of the AOK Nordost and Techniker Krankenkasse patients per year and of about 1,269 to 1,690 patients during the whole study period are possible.

For the secondary endpoints, which are patient-reported outcomes, an expected dropout of 30% was included in the calculations. Using a t-test with a two-sided type I error of 0.05, a mean difference of 0.20 (Cohen's d, small effect), and a case number of 841 patients (310 in the intervention group and 531 in the control group), a power of 0.80 was obtained. This calculation was performed using the software G*Power 3.1.9.7 [23].

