### Statistical analysis

The principal analysis focuses on the effect of the tele-neurological intervention, defined by the primary outcome, namely the proportion of neurologic problems being solved in the GPs’ practices, to answer the following question: *Do neurological teleconsultations in GP practices lead to an increase in the proportion of patients with neurological issues resolved in the GP practice in comparison to care as usual?*

A generalized linear mixed effects model will be used, in accordance with the sample size and power considerations above, to adjust for time-specific confounding and intra-cluster correlations. We assume time and intervention effects are common to all clusters, and model them as fixed effects. The random cluster effects allow accounting for intra-cluster correlation. Related sensitivity analyses will be described in the Statistical Analysis Plan.

We will report point estimates of the intervention effect along with 95% confidence intervals on absolute and relative scales (respectively measured as rate difference and rate ratio). Estimated correlations and time coefficients will also be reported.

The secondary analyses will assess the secondary outcomes and consist of testing the different study assumptions also using generalized linear mixed effects models (for secondary outcomes 1, 2, 4, 5, 6, 7), as well as a cluster-adjusted chi-squared test (for secondary outcome 3). For all analyses, we consider a significance level of 0.05.

The statistical analyses will be performed using R v4.2.2 (or higher, [24]). A comprehensive, detailed Statistical Analysis Plan, with details on handling missing values and ancillary analyses at individual and cluster levels, will be prepared before data locking and extraction for the statistical analysis.

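### The 80% power stated for the patient-reported secondary outcomes comes from a t-test on 310 versus 531 independent patients; the planned stepped-wedge model on the trial's own numbers gives about 49–59%

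*Protocol article*

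**What the plan says.** All statements are in the protocol article.

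- **Power for patient-reported outcomes** (Statistical methods: sample size and power calculations). The article says that "an expected dropout of 30% was included in the calculations". The method is given as "Using a t-test with a two-sided type I error of 0.05, a mean difference of 0.20 (Cohen's d, small effect"), run in G*Power, and the result as "a case number of 841 patients (310 in the intervention group and 531 in the control group), a power of 0.80 was obtained".
- **Target sample** (same section). The total is 1,089, "corresponding to 555 patients included in the control phase and 534 patients included in the intervention phase". Recruitment must reach "on average, at least 3 patients meeting the inclusion criteria, per cluster and step". The calculation for the primary endpoint uses the Hussey & Hughes stepped-wedge method with fixed time effects and random cluster effects.
- **Planned analysis** (Statistical analysis). The secondary outcomes are to be analysed "also using generalized linear mixed effects models (for secondary outcomes 1, 2, 4, 5, 6, 7"). Numbers 6 and 7 are quality of life and health status. The mixed model described there for the primary outcome has fixed time and intervention effects and a random cluster effect.
- **Layout** (Design; Sequence generation and intervention allocation). There are 33 clusters and 11 steps, all clusters start as controls, and all are in the intervention phase by step 11. Four clusters switch in the first, second-to-last and last sequences and three in each of the others.

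**The concern.** Two things do not fit together.

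First, the method. A t-test treats the patients as independent and estimates no period effects. In a stepped wedge, treatment is partly confounded with calendar time by design, so adjusting for period costs precision even with no clustering at all. The article allows for this for the primary endpoint and drops it one paragraph later.

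Second, the counts. A 30% loss applied to the stated target gives neither 841 patients nor a 37:63 split.

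Quality of life and health status carry much of the patient-level part of the objective. A reader told that a small effect is detectable with 80% power will take a null result as fair evidence against such an effect. If the true power is near one half, a real effect of d = 0.20 would be missed about four to five times in ten, not two in ten.

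**Working it through.** **1. Reproducing the stated figure.** Two-sample t-test, two-sided 0.05, d = 0.20, n = 310 and 531. The noncentrality is 0.20 × √(310 × 531 / 841) = 2.798, and the noncentral-t power is 0.798. This matches the stated 0.80, so the arithmetic of the t-test is right.

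**2. Checking the counts.**
- 1,089 × 0.70 = 762.3; 534 × 0.70 = 373.8 (intervention); 555 × 0.70 = 388.5 (control).
- 841 / 0.70 ≈ 1,201 enrolled. By arm, 310 / 0.70 ≈ 443 and 531 / 0.70 ≈ 759, against 534 and 555 stated.
- Differing dropout by arm does not explain the split: 531 of 555 controls would be a loss of only 4%.
- The same t-test with 374 and 388 gives 0.787, so the counts alone move the power little. The method is what matters.

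**3. Rebuilding the layout.** Ten sequences of 4, 3, 3, 3, 3, 3, 3, 3, 4 and 4 clusters over 11 periods give 363 cluster-periods, of which 185 are control and 178 intervention. At 3 patients each this is 555 and 534, exactly the stated split. With the Hussey–Hughes formula this layout also gives about 0.80 for the primary endpoint at a coefficient of variation of 0.25 and 0.82 at 0.20 (stated: 80% and 81%). The layout is therefore the sponsor's own.

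**4. Power under the stepped-wedge model.** With total variance 1, ICC ρ and m patients per cluster-period, set σ² = (1 − ρ)/m and τ² = ρ. Then

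Var = I σ²(σ² + Tτ²) / [(IU − W)σ² + (U² + ITU − TW − IV)τ²]

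where I = 33 and T = 11. U = 178 is the number of intervention cells. W = 3,990 is the sum over periods of the squared number of treated clusters. V = 1,260 is the sum over clusters of the squared number of treated periods. Hence IU − W = 1,884, and the bracket multiplying τ² is 10,828. Power is Φ(0.20/√Var − 1.96). A direct generalised least squares calculation agrees with the formula.

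For 762 analysed, m = 762.3/363 = 2.1:

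- ρ = 0: Var = 33 × 0.4762 / 1,884 = 0.00834; SE 0.0913; power Φ(2.19 − 1.96) = 0.59.
- ρ = 0.015: Var = 33 × 0.4690 × 0.6340 / (883.7 + 162.4) = 0.00938; SE 0.0969; power 0.54.
- ρ = 0.05: Var = 33 × 0.4524 × 1.0024 / (852.3 + 541.4) = 0.01074; SE 0.1036; power 0.49.

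The article gives no ICC for these outcomes, so these values are assumptions. The middle one borrows the primary endpoint's coefficient of variation: (0.25 × 0.20)² / [(0.25 × 0.20)² + 0.20 × 0.80] = 0.0025/0.1625 = 0.015.

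| Patients analysed | ICC 0 | ICC 0.015 | ICC 0.05 |
|---|---|---|---|
| 762 (1,089 less 30%) | 0.59 | 0.54 | 0.49 |
| 841, spread evenly | 0.63 | 0.58 | 0.52 |
| 1,089 (no loss) | 0.745 | 0.68 | 0.61 |

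**5. Source of the loss.** An equal-split t-test on 762 patients has variance 4/762.3 = 0.00525. The stepped-wedge variance is 1.59 times this at ICC 0, 1.79 times at 0.015 and 2.05 times at 0.05. Most of the inflation is the period adjustment, which is present at any ICC.

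**6. Detectable effect.** At 80% power, d = 2.80 × SE. With 762 analysed this is 0.26 (ICC 0), 0.27 (0.015) and 0.29 (0.05).

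**The case against.** The case for leaving the figure alone has four parts.

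- *It is not a miscalculation.* True: the article names the test, effect, counts and software, and the number follows from them. The fault is that the method does not match the design and the planned analysis, and that the counts do not match the target.
- *More patients may be available.* Three per cluster and step is a minimum, the article says all included patients can be analysed for these outcomes, and it projects 1,269 to 1,690 patients with complete data from the two participating insurers. The same model gives 0.81, 0.73 and 0.67 at 1,269 (ICC 0, 0.015, 0.05) and 0.90, 0.83 and 0.77 at 1,690. So recruitment above target would raise power. But the target is 1,089, and the stated 0.80 is tied to 841.
- *The EQ-5D-5L is also measured directly after the initial GP appointment.* Adjusting for that value could recover power: at 762 patients and an assumed correlation of 0.6, power is 0.78, 0.73 and 0.67; at 0.7 it is 0.87, 0.82 and 0.77. This is a real qualification. The 49–59% holds for a model without that covariate. The article states no such adjustment, though, and the published calculation used none.
- *Secondary outcomes need no power statement, and the planned confidence intervals will show the imprecision.* Also true. No sample size or decision rule depends on this paragraph. But a specific power was published, and readers will use it to interpret a null result.

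**Conclusion.** The concern holds. The 0.80 is right for a trial of 841 independent patients, which this is not. Under the only mixed model the article describes, with its own layout and its own 30% loss from 1,089, power for d = 0.20 is about 49% to 59% over ICCs of 0 to 0.05. Even the full 841 gives 52% to 63%, and all 1,089 with no loss reach at most 74.5% over that range. The conclusion does not hang on the assumed ICC, since the stated power already fails at ICC 0. It does assume roughly equal cluster-period sizes and no baseline covariate. The 841 and the 310/531 split also cannot be derived from the stated target, dropout and phase split. The primary-endpoint sample size is unaffected.

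**What to change.** Replace the paragraph with a stepped-wedge calculation for about 762 analysed patients (about 374 intervention and 388 control), using the same layout and model as for the primary endpoint. Report one of two things:

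- the power for d = 0.20: about 54% at ICC 0.015, with a range of 59% to 49% over ICC 0 to 0.05; or
- the detectable effect at 80% power: d of about 0.27, with a range of 0.26 to 0.29.

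Say that the ICC is an assumption and, if 0.015 is used, that it is carried over from the primary endpoint. Delete 841 and 310/531. If the sponsor intends to rely on baseline adjustment or on recruitment above 1,089, the paragraph should say so and give the correlation or number assumed.

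The cost is one rewritten paragraph and a less favourable figure. No patients are added, and neither trial conduct nor the planned analysis changes.

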### Sequence generation and intervention allocation

Following the considerations of a stepped-wedge design, GP practices were randomized to switch from the control into the intervention arm according to the pre-assigned dates of such a switch (see Fig. 1). The sequences to cross over from the control to the intervention arm were determined with a computerized randomization generator prior to the start of the trial by an independent investigator of the evaluation team. Except for the 1st, second to last, and last sequence in which 4 clusters will switch, each sequence is assigned to 3 clusters. All randomized clusters will be informed 4—6 weeks prior to their switch in order to prepare for the roll-out of the intervention. The entire randomization schedule of the clusters will not be shared with the participating clusters.

However, concealment of the sites and blinding of the GPs is not possible by the nature of the trial. Patients will only be aware of the allocation sequence after having given informed consent and once the GP discloses it to them. Then they will be aware of whether they are in the intervention or control group. Although data analysts will also not be blinded, we do not anticipate major bias to influence the analyzed effects.

### Statistical analysis

The principal analysis focuses on the effect of the tele-neurological intervention, defined by the primary outcome, namely the proportion of neurologic problems being solved in the GPs’ practices, to answer the following question: *Do neurological teleconsultations in GP practices lead to an increase in the proportion of patients with neurological issues resolved in the GP practice in comparison to care as usual?*

A generalized linear mixed effects model will be used, in accordance with the sample size and power considerations above, to adjust for time-specific confounding and intra-cluster correlations. We assume time and intervention effects are common to all clusters, and model them as fixed effects. The random cluster effects allow accounting for intra-cluster correlation. Related sensitivity analyses will be described in the Statistical Analysis Plan.

We will report point estimates of the intervention effect along with 95% confidence intervals on absolute and relative scales (respectively measured as rate difference and rate ratio). Estimated correlations and time coefficients will also be reported.

The secondary analyses will assess the secondary outcomes and consist of testing the different study assumptions also using generalized linear mixed effects models (for secondary outcomes 1, 2, 4, 5, 6, 7), as well as a cluster-adjusted chi-squared test (for secondary outcome 3). For all analyses, we consider a significance level of 0.05.

The statistical analyses will be performed using R v4.2.2 (or higher, [24]). A comprehensive, detailed Statistical Analysis Plan, with details on handling missing values and ancillary analyses at individual and cluster levels, will be prepared before data locking and extraction for the statistical analysis.

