### Outcomes

Outcomes pertain to the health care system (macro level), the institution (meso level) as well as the individual (micro level).

The primary outcome is the proportion of neurologic problems being solved in the GPs’ practices, measured by the number of patients without an outpatient referral (neurologic/other specialists), inpatient referrals (hospital), or other.

The secondary outcomes include on the macro level: (1) number of hospital stays, (2) length of hospital stay, on the meso level (3) number and types of referrals, and on the micro level (4) time until neurologic appointments, (5) time until specialty diagnostics, (6) quality of life, and (7) health status.

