There are several limitations to our study. This multi-center stepped-wedge design involving GP practices in the German public health care system can be vulnerable to secular trends, e.g., the COVID-19 pandemic and its impact on care. As with any trial in a real-world setting, we also expect a certain amount of missing information. However, these issues will be addressed with our analysis plan to account for such changes. Given the fact that the trial has to be integrated into the everyday care of the participating GP practices, only a finite number of parameters can be sampled to ensure uninterrupted workflow. However, our interdisciplinary approach during the evaluation planning phase, according to the Framework for Program Evaluation [30], involved clinicians (neurologists and GPs), biostatisticians, epidemiologists, health economists, and implementation specialists, which assured the necessary breadth of information to be collected. Due to local data protection regulations, no data on approached non-participant patients will be collected, thus limiting information on the representativeness of the reached population. This will be accounted for by providing detailed characteristics of the intervention participants.

The strength of NeTKoH is its pragmatic design, allowing for real-world evidence for a teleconsulting intervention in primary care accompanied by continued education for the participating GPs. Of note is that there will be no risk to the recruited patients and the trial will be monitored, and adverse issues will be reported.

Incorporating an evaluation of the implementation based on one of the most used approaches [31] will provide considerable information for policymakers to guide future use and possible scale-up of NeTKoH. Conducting a cost-effectiveness analysis will further provide key information for stakeholders.

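### The test named for referrals (secondary outcome 3) adjusts for clustering but not for calendar time, so a secular trend between earlier and later steps would bias it

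*Protocol article*

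**What the plan says.** The Outcomes section of the Protocol article lists, "on the meso level (3) number and types of referrals". It defines the primary outcome from the same information, "measured by the number of patients without an outpatient referral (neurologic/other specialists), inpatient referrals (hospital), or other".

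The Statistical analysis section uses a generalized linear mixed model for the primary outcome, "to adjust for time-specific confounding and intra-cluster correlations". It adds: "We assume time and intervention effects are common to all clusters, and model them as fixed effects". Six of the secondary outcomes are then to be tested "also using generalized linear mixed effects models (for secondary outcomes 1, 2, 4, 5, 6, 7"). For the remaining one, referrals, the same sentence names a different method: "as well as a cluster-adjusted chi-squared test (for secondary outcome 3"). Outcome 3 is the only one set apart. No time term and no stratification by step is given for its test. All analyses use a significance level of 0.05.

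The Design section has every practice start in control and has all of them in intervention by the start of the 11th step. The Discussion concedes that such a design "can be vulnerable to secular trends, e.g., the COVID-19 pandemic and its impact on care", and says in general terms that the analysis plan will account for such changes.

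**The concern.** In a stepped wedge the two arms are not observed over the same calendar time: control data come mostly from early steps and intervention data mostly from late ones. A cluster adjustment to a chi-squared test corrects the variance for patients within a practice resembling each other. It does nothing about a change over time in how often patients are referred, or where to. The article gives its primary model two tasks, time and clustering, and the test named for outcome 3 performs only the second.

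Referrals are the only meso-level outcome and, in the Objectives, the measure of effect on health care providers. A drift in referral habits during the pandemic could be reported as an effect of teleconsultation. Because the primary outcome is the absence of those same referrals, a time-adjusted primary result and an unadjusted referral result could point in different directions, each tested at 0.05.

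**Working it through.** **Inputs from the Protocol article.** 33 clusters and 11 steps (Design). Clusters per switching sequence 4, 3, 3, 3, 3, 3, 3, 3, 4, 4 (Sequence generation and intervention allocation). 3 patients per cluster and step, 555 control and 534 intervention patients, proportions 0.2 and 0.3, coefficient of variation (CV) 0.25 or 0.20 (sample size section).

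**1. Reproduce the stated figures.** Sequence s contributes s control steps.

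- Control cells: 4×1 + 3×(2+…+8) + 4×9 + 4×10 = 4 + 105 + 36 + 40 = 185.
- Intervention cells: 33×11 − 185 = 178.
- At 3 patients per cell: 555 and 534, exactly as stated.
- Hussey & Hughes power with fixed step effects, between-cluster SD = CV × 0.2, individual variance 0.25 × 0.75 and two-sided 0.05: the standard error is 0.0358 at CV 0.25 and 0.0350 at CV 0.20. Power is Φ(0.10/0.0358 − 1.96) = 79.8% and Φ(0.10/0.0350 − 1.96) = 81.6%, close to the stated 80% and 81%.

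The layout used below is therefore the plan's own.

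**2. Separation of the arms in time.**

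- Step numbers summed over control cells: 4×1 + 3×(3+6+10+15+21+28+36) + 4×45 + 4×55 = 4 + 357 + 180 + 220 = 761.
- Over all cells: 33 × 66 = 2,178. Over intervention cells: 2,178 − 761 = 1,417.
- Mean step: control 761/185 = 4.11; intervention 1,417/178 = 7.96; gap 3.85 steps.
- At 12 weeks per step the gap is about 46 weeks. If the 36 months and 17 days are divided evenly by 11, it is about 56 weeks.

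**3. Bias with no intervention effect.** For a linear trend, the spurious difference is trend × 3.85. Trends of 0.5, 1 and 2 points per step give 1.9, 3.8 and 7.7 points. The planned primary effect is 10 points.

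**4. False-positive rate, normal approximation.** Assumptions: proportion 0.3 and design effect 1.3 (the latter is not in the article).

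- SE = √[0.21 × (1/534 + 1/555) × 1.3] = 0.0317.
- 0.5 points: 0.0192/0.0317 = 0.61; Φ(0.61 − 1.96) + Φ(−0.61 − 1.96) ≈ 9%.
- 1 point: 0.0385/0.0317 = 1.21; about 23%.
- 2 points: 0.0769/0.0317 = 2.43; about 68%.

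**5. Simulation.** 3,000 trials per row on this layout, for a yes/no referral outcome with base rate 0.20, CV 0.25 and no intervention effect. Two versions of the chi-squared test were used because the article does not say which is meant. The comparator is a linear model with fixed step effects and a random cluster effect whose variance is taken as known. It is a simple stand-in for the planned mixed model.

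| Trend per step (points) | Mean difference, unadjusted (points) | Rejects: cluster-robust chi-squared | Rejects: ICC-adjusted chi-squared | Rejects: with step effects |
|---|---|---|---|---|
| 0 | −0.1 | 6.3% | 4.1% | 4.9% |
| +0.5 | +1.9 | 12.2% | 8.5% | 5.3% |
| +1 | +3.9 | 30.4% | 24.3% | 4.5% |
| −1 | −3.8 | 38.2% | 29.9% | 4.8% |
| +2 | +7.7 | 74.5% | 68.8% | 4.7% |

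With step effects the mean estimated effect was within 0.1 points of zero in every row.

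**The case against.** Several objections have weight.

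- **Scope.** This is one of seven secondary outcomes. The primary analysis has explicit fixed time effects, and the article promises to report its time coefficients, so a trend in the overall share of patients without referral would be visible. This stands and limits the harm. A trend within one referral type could still stay hidden.
- **Trend size.** The article gives none. One point per step is 10 points from step 1 to step 11; two points is 20, as large as the whole assumed control proportion. The upper figures are extreme cases. This stands, and all the rates are illustrations.
- **The unseen SAP.** It might stratify by step, and the Discussion says trends will be accounted for. But the article does not leave this test open: it names it and sets outcome 3 apart from the mixed models. A general statement does not alter a named test.

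Three stronger readings are tempting but not supported.

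- A reader might infer that every secular change is counted as an intervention effect. Only changes that shift the average between the two arms' time distributions bias the test; fluctuations that balance across them largely cancel.
- A reader might infer that a cluster-adjusted chi-squared test is unusable because each practice contributes to both arms. The version is not specified, survey-type corrections allow this, and without a trend the two versions reject at 6.3% and 4.1%.
- A reader might infer that the plan states time adjustment for every other outcome. It states it for the primary analysis. For the other six secondary outcomes it is implied by the reuse of mixed models.

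**Conclusion.** The point holds as a defect in one secondary analysis. The only test the article names for referrals has no time adjustment, in a design where control observations come on average 3.85 steps earlier than intervention observations, and although the article itself names secular trends as a risk. The gap follows from the stated layout with equal recruitment per cluster and step.

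The size of the bias depends on a trend the article does not give. For assumed linear trends of 0.5, 1 and 2 points per step, the spurious difference is about 1.9, 3.8 and 7.7 points, with false-positive rates of roughly 9–12%, 23–30% and 68–75% across the approximation and the two simulated tests. A falling trend of 1 point gave 30–38% in simulation.

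It should be corrected, but a reader should not infer that the trial's main conclusion or its power calculation is in doubt; neither depends on this test.

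**What to change.** Replace the chi-squared test for outcome 3 with the structure of the primary model: fixed step effects, a fixed intervention effect and a random cluster effect. Use a mixed logistic model for each referral type and a Poisson or negative binomial mixed model for the number of referrals. Allow sparse types to be combined, with the rule for doing so fixed in the SAP before data lock. Keep the chi-squared test as descriptive at most.

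In the same place, state that the mixed models for the other secondary outcomes carry the same step effects, which is at present only implied.

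The change takes about a sentence in the protocol and SAP and needs no new data. The cost is a little more analysis work, several per-type tests to interpret together, and possible convergence problems for rare referral types. Table 1 lists five destinations, and a single multinomial model would need about 4 × 10 = 40 period parameters with only about 3 patients per cluster and step. Separate models with sparse types combined are the safer choice.
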